## Abstract

**Background:**

Over the last three decades, overweight and obesity and the associated health consequences have become global public health priorities. Methods that have been tried to address this problem have not had the desired impact, suggesting that other approaches need to be considered. One of the lessons learned throughout these attempts is that permanent weight loss requires sustained dietary and lifestyle changes, yet adherence to weight management programs has often been noted as one of the biggest challenges. This trial aims to address this issue by examining whether social media, as a potential health promotion tool, will improve adherence to a weight management program. To test the effectiveness of this measure, the designated program will be delivered via the popular social networking site Facebook, and compared to a standard delivery method that provides exactly the same content but which is communicated through a pamphlet. The trial will be conducted over a period of twelve weeks, with a twelve week follow-up. Although weight loss is expected, this study will specifically investigate the effectiveness of social media as a program delivery method. The program utilised will be one that has already been proven to achieve weight loss, namely *The CSIRO Total Wellbeing Diet*.

**Methods/design:**

This project will be conducted as a 3-arm randomised controlled trial. One hundred and twenty participants will be recruited from the Perth community, and will be randomly assigned to one of the following three groups: the Facebook group, the pamphlet group, or a control group. The Facebook Group will receive the weight management program delivered via a closed group in Facebook, the Pamphlet Group will be given the same weight management program presented in a booklet, and the Control Group will follow the Australian Dietary Guidelines and the National Physical Activity Guidelines for Adults as usual care. Change in weight, body composition and waist circumference will be initial indicators of adherence to the program. Secondary outcome measures will be blood glucose, insulin, blood pressure, arterial stiffness, physical activity, eating behaviour, mental well-being (stress, anxiety, and depression), social support, self-control, self-efficacy, Facebook activity, and program evaluation.

**Discussion:**

It is expected that this trial will support the use of social media - a source of social support and information sharing - as a delivery method for weight management programs, enhancing the reduction in weight expected from dietary and physical activity changes. Facebook is a popular, easy to access and cost-effective online platform that can be used to assist the formation of social groups, and could be translated into health promotion practice relatively easily. It is anticipated in the context of the predicted findings that social media will provide an invaluable resource for health professionals and patients alike.

**Trial registration:**

Australian New Zealand Clinical Trials Register (ANZCTR): ACTRN12614000536662. Date registered: 21 May 2014.

**Electronic supplementary material:**

The online version of this article (doi:10.1186/s12889-015-1849-4) contains supplementary material, which is available to authorized users.

## Background

World-wide rates of overweight and obesity continue to rise, despite the growing awareness of the importance of this issue in recent years among health professionals [1–4] as well as the general public [5]. Indeed, there is a widespread lack of acceptance of obesity in the general community, perhaps relating more to the physical appearance of people with obesity rather than the associated health risks [5, 6]. It is also well-established that being socioeconomically disadvantaged increases the risk of overweight and obesity [7]. The health consequences of excessive weight gain include an increased risk of the metabolic syndrome, and such chronic diseases as diabetes, cardiovascular disease, obstructive sleep apnoea and some cancers, all potentially leading to increased mortality [2, 4]. The psychosocial consequences of obesity include stigmatisation in the workplace, compromised health care and personal relationships [5, 8] and reduced quality of life [4, 8].

A review of the relevant literature has revealed that an energy-restricted, low fat, high protein diet assists with weight loss [9, 10] and the reduction of cardiometabolic risk factors [11]. It also increases satiety [12], which is an important factor in dietary compliance [13], and assists with weight loss maintenance [12]. Increasing physical activity has also been shown to improve cardiometabolic risk factors in both short and long- term trials [14, 15]. According to the National Physical Activity Guidelines for Adults, thirty minutes of moderate physical activity (preferably taken every day) is required to promote health [16].

The CSIRO Total Wellbeing Diet (TWD), developed by the Commonwealth Scientific and Industrial Research Organisation (CSIRO) [17], is an energy-reduced, low fat, higher protein diet that meets the Australian nutrient reference values for daily intake [18], promotes a minimum thirty minutes of moderate physical activity per day, and has been extensively researched [9, 11, 19, 20]. In Book 2 of the TWD, the use of a pedometer is recommended to help individuals meet the suggested physical activity target [17]. Pal et al. have shown that setting a goal of 10,000 steps per day results in greater improvements to physical activity levels than the 30-min-a-day target [21]. This weight management program, along with the support of a dietitian, has been shown to cause significant improvements in cardiovascular disease risk biomarkers in overweight and obese individuals and weight loss of up to 10 kg after twelve weeks [11, 20]. However a mean weight loss of 5 kg has been reported by individuals following the TWD Book alone [22].

While weight loss can reduce the health risks associated with obesity [12, 23], many dieters have difficulty adhering to weight loss programs [24] or maintaining long-term weight loss [12, 23]. This can contribute to a sense of personal failure [6]. However, the lack of successful long-term weight loss in overweight and obese individuals may be due to the format of the weight management programs, such that dietary and lifestyle recommendations alone may not be enough [8]. In fact, the high attrition rate and/or weight regain after initial weight loss is so common that many researchers have tried to address this key issue by also adding other components to the treatment or intervention [22]. For example cognitive behavioural therapy, group support sessions, frequent medical or clinical appointments with health professionals and dietary supplements are additional strategies that have been included in some weight management programs or trials [4, 7, 25]. Research indicates that a multifactorial approach is likely to be optimal in achieving clinically meaningful weight loss results [22].

Another factor that is frequently overlooked in identifying adequate treatment for overweight and obesity is cost effectiveness [26]. If the socioeconomically disadvantaged are some of the worst affected in the obesity epidemic, then some of the more expensive commercially available weight loss programs (such as Weight Watchers™) [7] or strategies will probably not be an option for them. However, the evidence suggests that some form of social support yields better weight loss results than ‘going it alone’ [6]. It has also been clearly established that individuals can expect better health outcomes if they are well supported in a social sense [27, 28]. However, many individuals attempting weight loss don’t always receive the required social support for a variety of reasons [28].

Advances in internet communication technology in recent years have added another vehicle for the delivery of health promotion material, including weight loss programs. According to recent survey data, 99 % of Australian households have internet access, 69 % of Australians use social media and 95 % of these social media users have a Facebook account [29]. Almost 99 % of the population is covered by a mobile cellular network and there are 102.8 mobile cellular subscriptions for every 100 Australians [30]. This offers health promoters the opportunity to deliver cost-effective weight management programs. Internet-mediated social networking [31] increases this potential, as studies have shown that social media can provide social support to members [32] by motivating and inspiring one another. Social media can also offer a medium for information sharing [33]. Being a part of an online social community undergoing lifestyle modifications may even assist individuals to be more accountable for their progress, and improve motivation further. Moreover, a review of the literature indicates that online health improvement programs often result in positive change [34–36]. A number of internet-based health intervention studies have utilised an interactive or social element, such as discussion boards or chat rooms, with many providing tailored feedback generated via mobile monitoring devices or health professionals [37, 38]. To date there have been few studies that have examined the effectiveness of using the social media platform (such Facebook) in the area of weight management, and none promoting dietary *and* physical changes *without* providing feedback other than the support derived from other study participants [37, 38].

### Aim of this study

The aim of this project is to measure weight loss and other outcome measures in overweight and obese individuals when a weight management program is delivered via social media, compared to the same program presented in written information only. The study will be undertaken over a period of twelve weeks, with a twelve-week follow-up thereafter. This trial will: i) determine whether incorporating social media into a weight management program will assist overweight and obese individuals to achieve greater, more sustainable improvements in weight loss and other outcome measures than following the same dietary and lifestyle recommendations in written form alone; ii) elucidate the particular aspects of social media that assist overweight and obese individuals to achieve the greater improvements in weight loss and other outcome measures.

### Summary of intervention

One hundred and twenty overweight and obese participants from the Perth community will be enrolled into the study, and randomly divided into three groups: two intervention groups and a control group. The two intervention groups will be instructed to follow the CSIRO TWD [17] weight management program for the twelve-week intervention period. One of the intervention groups will receive the diet via the social networking website Facebook and will be enrolled into a support network which is hosted via the Facebook site. The other group will receive the intervention in written form (pamphlet) alone. Both of the intervention groups will be supplied with pedometers (G Sensor 2025 Accelerometer, Walk with Attitude Australia) and set a target of 10,000 steps per day. The control group will follow the Australian Dietary Guidelines [39] as well as National Physical Activity Guidelines for Adults [16] as usual care. Participants will complete a series of questionnaires which will evaluate key psychological variables (see below) and attend Curtin University for assessment of body weight and other clinical outcome variables (outlined in the Design/Methods section) at weeks 0, 6, and 12 and at further 12-week follow-up (week24). The primary outcome measures in this trial include weight, body composition and waist circumference. Blood glucose, insulin, blood pressure, arterial stiffness [40], physical activity, eating behaviour, mental well-being (stress, anxiety, and depression), social support, self-control, self-efficacy, Facebook activity, and program evaluation are secondary outcome measures. Changes in psychological and clinical outcomes are expected to be greatest in the intervention group delivered and supported by social media relative to the pamphlet intervention and control groups. It is anticipated that social media will provide an invaluable resource for health professionals, serving as a low maintenance vehicle for communicating with patients and a source of social support and information sharing for individuals undergoing lifestyle modifications.

### Hypotheses

In the present study, it is hypothesised that, compared to the Control Group, the Pamphlet Group will experience moderate improvements in outcome measures (including weight loss of approximately 2 kg) as a result of the twelve-week pamphlet-delivered intervention. It is also hypothesised that, compared to the Control Group, the Facebook Group will experience greater improvements in outcome measures (including weight loss of approximately 8 kg) as a result of the twelve-week social media-delivered intervention. It is further hypothesised that participants in the Facebook Group will experience greater improvements in outcome measures compared to the Pamphlet Group due to the support they receive from using Facebook. Finally, it is hypothesised that at the expiration of the twelve-week intervention period the Facebook Group will be self-sustaining with respect to their ongoing stable weight.

## Methods/design

### Participants

A cohort of 120 overweight and obese individuals with a body mass index (BMI) between 25–40 kg/m^2^ and aged between 21 and 65 years will be recruited from the Perth community via flyers posted at community noticeboards, advertisements in local newspapers and advertisements on local community radio stations. Eligible participants will also be required to have access to a computer, laptop, tablet or Smartphone. Exclusion criteria will include smoking, lipid lowering medication, use of steroids and other agents that may influence lipid metabolism, use of warfarin, diabetes mellitus, hypo- or hyperthyroidism, cardiovascular events within the last 6 months, major systemic diseases, gastrointestinal problems, proteinuria, liver disease, renal failure, weight fluctuations over the past 6 months, vegetarianism or participation in any other clinical trials within the last 6 months. All participants will be required to provide written informed consent before the trial commences. All identifiable information from participants will be coded. This study will be conducted according to the ethical guidelines that are specified in the Curtin University Human Research Ethics Committee (HREC) and the National Health and Medical Research Council (NHMRC) guidelines. This trial has been approved by the Curtin University HREC (approval number: HR90/2014) and has been registered with ANZCTR (registration number: ACTRN12614000536662), on 21 May 2014.

### Study design

This will be a three-armed, randomised, controlled, parallel design intervention study undertaken over a 12 week period, with a subsequent 12 week follow-up. Interested participants will be screened according to the inclusion/exclusion criteria and those eligible will be allocated a number, stratified according to age and gender, and then randomly allocated to one of the three groups of 40 participants, using dedicated computer randomisation software [41, 42] The allocated number will also be used as the participants’ identification number, to be used on all records and questionnaires. The three groups will consist of: the Control Group who will follow the Australian dietary guidelines [39] and National Physical Activity Guidelines for Adults [16], the Pamphlet Group who will be instructed in the weight management program by written information, and the social media group who will receive exactly the same weight management program via Facebook in the Facebook Group. [Please see Fig. 1: Flow of participants.] The initial twelve-week weight management program will be presented to the two intervention groups as a condensed version of the CSIRO TWD [17], which includes information of the weight management program, along with weekly checklists available from the CSIRO TWD [43]. Before the commencement of the trial, participants will attend an information session specific to their group allocation, where the participation requirements, including questionnaires and outcome measurements, will be explained. An additional file explains this in greater detail [please see Additional file 1]. During the Facebook Group information session, participants will be provided with additional information about using Facebook in this context. Facebook Group participants will also be made aware of the role of the primary investigator as administrator and facilitator of the Facebook Group. In addition, participants in this group will be informed that at the completion of the twelve-week intervention period, all facilitation will cease, however the group will still be monitored by the facilitator to ensure that they continue to conduct themselves according the instructions provided. This change in strategy for the twelve-week follow-up period will be used to determine whether the Facebook Group has become self-sustaining. An additional file explains the added information provided for Facebook Group participants in greater detail [please see Additional file 2].

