### Assessments

All participants will be required to attend regular clinical appointments for a duration of approximately 15 min, as follows: at baseline, at weeks 6 and 12, and then again for a follow-up appointment at week 24. Prior to each appointment, participants will complete a Three-Day Food Record and selection of questionnaires to monitor compliance and address some of the secondary outcome measures. The Bouchard Three-Day Physical Activity Record [44] will be used to measure of total physical activity. The Three-Factor Eating Questionnaire (TFEQ) [45] will provide a measure of dietary restraint, disinhibition and hunger, and will also be used here to assess changes in satiety. The Self-Efficacy Scale [46] will be used to assess changes to participants’ self-efficacy. The WHO Quality of Life Questionnaire [47] will be used to determine changes in participants’ quality of life. The short version of the Depression Anxiety Stress Scale (DASS 21) [48] will be used to measure changes in general psychological wellbeing. The Self-Control (Brief) Scale [49] will be used to provide an understanding of participants’ impulse control as it relates to eating behaviour. The Diet and Physical Activity Survey, constructed using the Theory of Planned Behaviour [50], will be used to determine participants’ intentions with regard to the dietary and physical activity guidelines being used in the trial. The Survey of Weight Management Program has some general questions regarding the ease of use of the dietary and physical activity guidelines being utilized; there will be an extra section for Facebook Group participants to assess the preferred device for accessing the weight management information provided on Facebook. For Facebook Group participants only, the Social Media Survey will be used to assess participants’ attitudes to social media. The final questionnaire will also be administered to Facebook Group participants only; the Facebook Intensity and Network Density Scales contains a combination of questions used in previous social media research [51, 52]. It will be adapted for this study to assess the degree to which participants make use of Facebook, as well as the strength and frequency of the social interactions within the Facebook Group. In addition, the Facebook Group page will be printed at the end of each week to corroborate self-reported Facebook usage data and monitor participants’ online behaviour. Participants will be given questionnaires (including the Food Record and Physical Activity Record) at each clinic appointment, according to their group allocation. [For further information regarding the assessments please see Table 1: Schedule of Assessments.] Participants will be instructed to use their participant identification number only when completing all documents relating to this trial [42].

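### Week-0 measures appear to be taken after participants know their arm, so the baseline, above all self-report, is not protected from knowledge of allocation

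*Protocol article*

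**What the plan says.** Four places in the protocol article bear on the order of events.

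- **Study design, allocation.** The step after screening is given as "those eligible will be allocated a number, stratified according to age and gender, and then randomly allocated to one of the three groups of 40". No baseline measurement is mentioned between screening and allocation.
- **Study design, session.** "Before the commencement of the trial, participants will attend an information session specific to their group allocation". This is the session "where the participation requirements, including questionnaires and outcome measurements, will be explained". The Facebook arm gets more: "During the Facebook Group information session, participants will be provided with additional information about using Facebook in this context".
- **Assessments.** Clinic visits take place "at baseline, at weeks 6 and 12, and then again for a follow-up appointment at week 24". The rule for self-report is this: "Prior to each appointment, participants will complete a Three-Day Food Record and selection of questionnaires". The forms are given out "at each clinic appointment, according to their group allocation".
- **Table 1.** Eight self-report instruments are marked at week 0 in all three arms. The Social Media Survey is marked at week 0 for the Facebook Group alone.

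Statistical analysis plans a mixed repeated measures ANOVA. Outcome measures lists weight loss, body composition and waist circumference as primary.

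**The concern.** Randomisation makes the arms alike, apart from chance, on anything measured before the arm is revealed. It gives no such assurance for a measure taken afterwards. A participant who has just been assigned to usual care, or to a supported online group, may answer questions on mood, self-efficacy, intentions or recent eating differently for that reason alone, with no change in behaviour. Food and activity records have a further weakness: both what is done and what is written down can change over the recording days.

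At stake is the meaning of change from week 0. If the arms differ at week 0 because of disclosure, that difference is built into every later comparison with baseline. Analysis cannot recover an unaffected baseline afterwards. The aim is to compare ways of delivering one programme, so reactions to learning which delivery one has been given are a plausible source of such a difference.

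**Working it through.** The plan gives no figure to reproduce here. The check is of sequence, followed by how a shift would pass through the analysis.

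**Step 1: is the arm known at week 0?**

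- Study design puts allocation straight after screening and names no measurement in between.
- The arm-specific session comes before the trial commences. Attending it tells participants their arm.
- The session explains the questionnaires and measurements, which makes most sense if it comes before the first of them.
- Table 1 has a week-0 form for the Facebook Group only. It cannot be issued at week 0 unless allocation has already been made and acted on.

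The first, second and fourth items come from the text or the table. The third is inference. Together they show that the arm is in use at week 0. They make it likely, though not explicit, that disclosure precedes every week-0 measure.

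**Step 2: which measures are exposed?**

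- *Directly, through reporting:* the eight self-report instruments given to all arms at week 0, namely the food record, physical activity record, Three-Factor Eating Questionnaire, Self-Efficacy Scale, WHO Quality of Life, DASS 21, Self-Control Scale, and Diet and Physical Activity Survey. The last asks about intentions towards the guidelines used in the trial. Those differ between Control and the two intervention arms, so if it refers to a participant's own guidelines, its score depends on the arm.
- *Only if behaviour changes first:* weight, waist, body composition and the other clinic and blood measures.

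**Step 3: how does a shift enter the analysis?**

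Let s_F and s_P be the average shifts at week 0 caused by knowing the arm (Facebook, Pamphlet), and let D be the between-arm difference in change that an undisturbed baseline would give. Assume that later visits are unaffected by s.

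- Contrast at any later visit t against week 0: observed = D_t − (s_F − s_P).
- The same term, s_F − s_P, enters at weeks 6, 12 and 24, because all three use the same week 0.
- Equal shifts cancel: s_F = s_P gives observed = D_t. Only an arm-dependent shift matters.
- If all four visits enter as time levels, the group main effect averages over them and carries (s_F − s_P)/4.

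For weight, the Hypotheses section expects losses of about 8 kg and 2 kg against Control, so D = 8 − 2 = 6 kg. This agrees with the 6 kg in Statistical analysis. If e_F and e_P are the losses before week 0, the observed contrast is 6 − (e_F − e_P). Early loss in the Facebook arm alone would therefore dilute the contrast, not inflate it. For self-report the direction could go either way.

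The document gives neither the shifts nor the interval between disclosure and week 0, so no number follows.

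**The case against.** The strongest case on the other side is that the full order is never stated. No sentence places the session before every week-0 measure. Forms are completed before each appointment yet handed out at appointments, so the handling of the first set is unclear. BMI is an eligibility criterion, so some measurement might precede allocation. The participant flow figure and the additional files, which may settle the order, are not available here. The primary outcomes are measured, not self-reported, and participants know their arm at every later visit in any case.

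Much of this stands as a limit on the point. It does not remove it: the Facebook-only form at week 0 shows allocation in use at baseline, whatever the exact day of the session. Knowledge of the arm at later visits is unavoidable in this design. Knowledge at baseline is avoidable, and baseline is the one occasion on which the arms can be compared before disclosure.

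A reader might also infer more than the document supports:

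- *That week 0 is not a pre-treatment measure.* The session is described as explaining participation and, for one arm, the use of Facebook. Nothing says that the diet, the step target or the Facebook group begins before week 0.
- *That consent is taken after the arm is known.* The text says "All participants will be required to provide written informed consent before the trial commences", which does not fix its timing relative to allocation.
- *That baseline is spoiled as a covariate.* No baseline covariate is planned in the text shown.
- *That people disappointed with their arm leave before baseline.* No document gives such losses.
- *That some number of kilograms is lost before week 0.* Any such figure would be invented.

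**Conclusion.** The point holds as a weakness in the order of procedures. As described, week-0 measures appear to be collected with the arm already known, so the baseline is not protected from knowledge of allocation. The concern is clearest for the self-reported secondary outcomes. For weight, waist and body composition it depends on behaviour changing between disclosure and week 0, which the document neither states nor rules out.

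The size cannot be estimated. What can be said is structural: an arm-dependent shift at week 0 carries over one for one into each group-by-time contrast with baseline, while a shift common to the arms cancels.

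This rests on two assumptions: that the session precedes the week-0 measures, which is a strong inference, and that week 0 is a time level in the ANOVA, which is the natural reading. It should be corrected because visit order is something the protocol itself sets and the change is cheap.

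**What to change.** Adopt this order and state it:

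1. Complete the week-0 food and activity records, questionnaires and clinic and blood measures that are common to all three arms. The explanation of questionnaires and measurements that now sits in the arm-specific session would need to be given beforehand, in the same form to everyone.
2. Disclose the allocation.
3. Hold the arm-specific session, and give the Facebook-only Social Media Survey then. It is used within one arm, so collecting it after disclosure affects no between-arm comparison. Extending it to all arms is a matter of preference and is not needed for this point.

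Amend Study design, Assessments and Table 1 to match, including how the first set of forms reaches participants before the week-0 visit. If baseline is in fact already taken before disclosure, the sponsor should say so and reconcile those three places.

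The cost is that disclosure and the arm-specific session move slightly later, and scheduling needs some rearranging. No new instrument is required.
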